### Recruitment and Management of Participants

#### Rollout

After written approval from the ethics or education authority has been received, local study coordinators (LSC) will visit each school to obtain the head teacher’s permission to attend schools to deliver the 21-day BDN program and collect data. The LSCs are also responsible for the full delivery of the program from recruiting and matching the schools and composing the dental teams to training the teachers. A dental team is generally composed of 2 to 4 trained and certified dentists and nurses. Dentists will also receive appropriate training and be calibrated for the oral health examinations. A trained and calibrated dental team will be responsible to collect the answers from the self-reported questionnaire and complete the clinical observation of oral health statuses recording the plaque index at all study end points and the caries DMFT index at baseline and at the end of the study (T2). In addition, the LSC will be in charge of training the teachers to deliver the 21-day BDN program over 21 days.

The LSC will be given a list of unique user IDs generated for each school, for each class, and for each child participating in the program. The head teacher will be asked by the LSC to provide a list of the children attending years 1, 2, and 3 in their schools. The list should include first and last name, gender, and date of birth (dd/mm/yyyy) for each child plus the name of the child’s parent.

A member of the study staff will explain the details of the study in person to parents. If parents wish their child to participate, the parent will sign the appropriate informed consent form. Two copies of the informed consent will be completed, one copy will be kept by the parents and one copy returned to the national dental association team. Each LSC is responsible for leading the dental teams. The LSC will assign an ID to each child participating in the study. This ID only plus the exact date of birth will be used to report data, so the data collected will be anonymous once reported.

#### Selection Criteria

A list of inclusion and exclusion criteria will be defined to manage participants in the study. Children in school year grades 1, 2, and 3, aged 6 to 9 years, in good general health, willing and able (eg, to brush teeth and understand and respond to questions) to participate in the 21-day BDN activities at school and at home, and planning on attending their currently registered school for at least the next 12 months will be included.

Exclusion criteria include failure of parents to provide written informed consent, children scheduled for medical or dental procedures during the duration of the study, children who have a known allergy to any toothpaste ingredients, children with obvious signs of gross or untreated caries or of significant periodontal disease which in the opinion of the dentist would affect the scientific validity of the study, or children whose well-being would be affected by the study. Children and their families should have no affiliation (eg, employee) with either FDI or Unilever.

#### Participant Restrictions

A list of restrictions is also set on participants, such as children should not take part in any other form of oral health education for the duration of the study (ie, those that might be delivered at community health centers). Parents should inform their child’s class teacher if they receive any form of dental treatment during the study duration or if they have been prescribed any medicines.

#### Participant Withdrawal

Participants can withdraw from the study at any time, and parents will be advised at the start of the study that they may withdraw their child and family from the study at any time without giving a reason. If a parent withdraws a child from the study, the parent will also be considered withdrawn. Children will be withdrawn from the study analysis if they miss more than 5 days of school during the 21-day intervention period. School attendance during the 21-day period will be checked against the school register.

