### Data Management

#### Data Exclusion

All school data will be used, and where a school has been significantly noncompliant (eg, a school has not sufficiently followed and completed all elements of the 21-day BDN program) with the protocol, this will be registered. Minor deviations may be included at the discretion of the LSC. Participants who missed more than 5 days (one school week) of the 21-day BDN program will have this information registered in the analysis.

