### Statistical Analysis

As outlined in Table 2, five outcomes measures have been prepared and prioritized to evaluate the effect of the 21-day program. At each time point, summary statistics will be calculated for intervention and control schools and include within- and between-group analyses.

Each of the mentioned measures in Table 2 will be compared between T0 and T0+21 and between T0 and T0+21 and T1 and T2 for the intervention and control groups. The mean change will be reported, with 95% confidence interval and associated *P* value. Longitudinal models will be used. Multinomial logistic regression will be performed when the outcome variables have a nominal level of measurement. For ordinal and interval outcome variables, we will use either ordered logistic or linear regression as appropriate. To measure positive change, we will convert nominal or ordinal independent variables using dummy variables where each dummy will be measuring the effect of one answer category on the reference category.

Each of the above measures will be compared between the intervention and control group at T0, T0+21, T1, and T2 using analyses of covariance, mixed models, and generalized estimating equations as appropriate. Mean differences will be reported, with 95% confidence interval and associated *P* value.

In addition to analyzing the impact of the program on various beneficiaries through behavior and health change, the global impact of the 21-day program will be analyzed. This analysis will be performed by multivariate analysis, which measures the influence of each outcome variable on the others and of each independent variable on the relevant outcome variables. We will also measure some of the variables with a measurement model such as factor analysis. All statistical analyses will be performed using SPSS Statistics software.

To minimize bias in the results, the intention to treat principle will be applied and every randomized participant will be analyzed. The school structure is helping us to minimize missing data, but it may still occur due to the longitudinal aspect of the study and number of follow-ups. In this case, carrying the last data forward should be the best approach.

**Table 2 table2:** Study objectives as they relate to the statistical analysis plan.

Objective	Outcome variables	Results observed for	Hypotheses

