Quaternary: provide evidence that the 21-day school program is effective in getting parents and carers to also improve their brushing habits and to brush day and night.	Parent questionnaire: reported brushing frequency, reported use of fluoride, renewing toothbrush frequency, amount of purchased toothpaste	within-group analysis: T0+21 vs T0; between-group analysis: T0, T0+21	Consenting for their children to participate in a toothbrushing program will likely trigger a reflection upon their own oral care habits, and parents’ own brushing frequency, use of fluoride toothpaste, amount of toothpaste, and toothbrushes purchased should increase when compared with baseline and compared with parents in the control group.
Quinary: measure the change in quality of life, well-being, and social measures of school children after a 21-day oral health program	Child questionnaire: reported absenteeism for oral health issues	within-group analysis: T0+21 vs T0; between-group analysis: T0, T0+21	Children may report less dental discomfort/pain and a need to take fewer days off school as a result.

^a^OHI-S: Simplified Oral Hygiene Index.

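### Removing children from the analysis for missing more than 5 school days contradicts the stated intention-to-treat analysis and conditions the primary comparison on post-randomisation attendance

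*Protocol article*

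**What the plan says.** Three sections of the protocol article deal with a child who is often absent during the 21 days.

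- **Participant Withdrawal:** "Children will be withdrawn from the study analysis if they miss more than 5 days of school during the 21-day intervention period". The trigger is the register: "School attendance during the 21-day period will be checked against the school register".
- **Data Exclusion:** "All school data will be used", and "Participants who missed more than 5 days (one school week) of the 21-day BDN program will have this information registered in the analysis". No removal of a child is stated here. The section adds: "Minor deviations may be included at the discretion of the LSC".
- **Statistical Analysis:** "the intention to treat principle will be applied and every randomized participant will be analyzed".

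Table 2 in the Statistical Analysis section lists the quinary outcome as "Child questionnaire: reported absenteeism for oral health issues". It is compared within groups between T0 and T0+21, and between groups at those two points. The stated hypothesis is that children will need fewer days off school.

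**The concern.** The analysis set decides which children produce the primary result, and the article defines it in two incompatible ways. This is not detail left to a separate analysis plan: the article commits itself on the point, and its commitments conflict.

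The withdrawal rule acts on something observed after allocation. Schools are randomized, the 21 days run, and only then is a child kept or dropped according to attendance. Attendance could differ by arm because of the program itself, which includes stickers, a closing celebration and rewards (Intervention section). The sponsor's own quinary hypothesis is that the program reduces days off school. If attendance differs by arm, or if the frequent absentees differ in kind, the children left in the two arms are no longer comparable by randomization. The T0+21 comparison, which is the primary one, comes directly after this selection, and every later comparison inherits it.

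If the conflict stays open, the choice between the two sets could be made after the data have been seen.

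**Working it through.** **1. Can the statements be reconciled?** Take a child enrolled in a randomized school who misses 6 school days in the window.

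| Section | What happens to the child |
|---|---|
| Participant Withdrawal | Removed from the analysis |
| Data Exclusion | Kept; absence registered |
| Statistical Analysis | Analysed |

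The last two rows agree with each other, and the first contradicts both. It cannot be read as ordinary withdrawal of consent, because it names the analysis and is triggered by the register, not by a parent's decision.

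**2. Whom does the rule remove?** The Prior Work section equates 21 calendar days with 15 school days, so the rule removes children with 6 to 15 absent days. The article gives no expected share of such children, so everything in steps 3 to 5 rests on assumed shares.

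**3. What could it do to the primary comparison?** Suppose there is no true effect. Let *p* be the twice-daily brushing rate among all children in each arm, *q* the rate among excluded children, and *e* the excluded fraction. The rate observed in the children who remain is

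(p − q·e) / (1 − e).

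Assume p = 0.60 and q = 0.35.

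- e = 0.15: (0.60 − 0.0525)/0.85 = 0.5475/0.85 = 0.644
- e = 0.05: (0.60 − 0.0175)/0.95 = 0.5825/0.95 = 0.613
- Apparent difference: 0.644 − 0.613 = 0.031, or 3.1 points in favour of whichever arm loses more children.
- e = 0.10 in both arms: (0.60 − 0.035)/0.90 = 0.628 in each, difference 0.

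**4. How far does this depend on the assumptions?** With p = 0.50 and excluded children 20 to 40 points lower (q = 0.30 or 0.10):

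| Excluded, arm A vs arm B | Apparent difference (A − B) |
|---|---|
| 10% vs 5% | 1.2 to 2.3 points |
| 20% vs 10% | 2.8 to 5.6 points |
| 10% vs 10%, same q | 0 |

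Equal fractions alone do not guarantee zero. With 10% excluded in each arm but q = 0.10 in one and 0.30 in the other, the remaining rates are (0.50 − 0.01)/0.90 = 0.544 and (0.50 − 0.03)/0.90 = 0.522, a difference of 2.2 points.

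**5. Is power the issue?** Hardly. Take Indonesia's 40% against 70%, 10 schools per arm, an assumed 30 children per school and an intraclass correlation of 0.10 (the upper value the article names, for Nigeria). A normal approximation with the usual design effect gives power of 96.9% with nobody excluded and 96.1% with 20% excluded. The matter is possible bias, which a larger sample does not remove.

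**6. Absenteeism outcome.** The rule counts all-cause absence in the register. The outcome is self-reported absence for oral health reasons, and the recall period of that question is in an appendix not shown. The two overlap but are different variables. Some children with high reported absence at T0+21 may be removed; how many cannot be calculated from the article.

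**The case against.** The strongest reply is that two of the three sections already give the intention-to-treat answer, including the one headed Data Exclusion, so one stray sentence stands against the rest. That is fair as to which reading should prevail. It does not remove the conflict: the sentence is explicit, and an analyst could follow it in good faith.

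The second reply is that the rule is symmetric. This stands in part. The sentence counts days of school against a register that both arms have. A reader might infer from Data Exclusion, which counts days missed of the program, that only intervention children can be dropped. The documents do not support that, because the program-based count belongs to a statement that registers absence and excludes nobody. Scenarios with no exclusions among controls therefore model a rule the article does not contain. Symmetric wording still does not ensure symmetric exclusion when attendance may respond to the program.

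A reader might also infer that the effect is inflated. That is not established. If the program improves attendance, more control children would be dropped, and under the same assumptions the sign in step 3 reverses.

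On absenteeism, it would go too far to say the outcome cannot show its largest values, for the reason in step 6.

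Finally, the sentence on the local study coordinator's discretion might be read as letting the person responsible for delivery decide which data count. It is ambiguous: it follows a statement that all school data are used, and may concern only which minor deviations are recorded. It needs clarifying but does not show a power to drop data.

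**Conclusion.** The contradiction is certain and rests on the text alone. If the attendance rule is followed, the stated intention-to-treat analysis is not carried out and the primary comparison is no longer fully as randomized.

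The numerical consequence is not known. The 3.1 points rest entirely on assumed exclusion fractions and brushing rates. Against the differences of 30 and 35 points the trial is designed to detect, that is about a tenth (3.1/30 = 10%; 3.1/35 = 9%), so on those assumptions it would not by itself create an effect of the planned size. It could still shift the estimate and its confidence interval in either direction. The effect on the absenteeism outcome is plausible, of unknown extent, and confined to a low-ranked outcome.

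The point still needs correcting, because it concerns the definition of the primary analysis set and a choice that should not remain open once data are available.

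**What to change.** - **Participant Withdrawal:** delete the sentence that withdraws children from the analysis on attendance. Leave the right of parents to withdraw a child at any time unchanged. Keep the register check as data collection.
- **Statistical Analysis:** state that all enrolled children in all randomized schools are analysed in the arm of their school, whatever their attendance, and that the absenteeism outcome is analysed on the same full set. A child not measured at a time point is then a missing-data case, not an exclusion.
- **Data Exclusion:** define the absence flag as register days of school, over the same window and in the same way in both arms. Use it only for a supportive per-protocol sensitivity analysis. State that the local study coordinator's discretion over minor deviations does not decide whether data enter the primary analysis.

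The cost is wording only; no extra children, visits or measurements are needed. The estimate may be slightly diluted by low attenders, but that is the effect an intention-to-treat analysis is meant to capture, and the per-protocol analysis will show how much it matters.

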## Introduction

### Prior Work

The Brush Day & Night (BDN) program is the result of a 12-year partnership between FDI World Dental Federation (FDI) and Unilever. It is an intense education activity designed to establish the habit of brushing day and night with a fluoride toothpaste. The program involves daily brushing instruction and includes free toothpaste and toothbrushes (see Multimedia Appendix 1 for more information).

The program was designed based on the theories of behavior change. Behavior change interventions and the formation of health promoting habits is thoroughly reviewed by Lally et al [1] and specifically in the context of interventions to improve tooth brushing by Claessen et al [2]. This and other research was crystallized into the Unilever 5 levers of change model [3], which is the foundation for the design of this particular intervention. The first step of the model is to identify barriers, triggers, and motivators to adopting a new behavior. Those insights are considered in designing a new behavioral intervention in 5 steps:

Make it understoodMake it easyMake it desirableMake it rewardingMake it a habit

This is a 21-day intervention, a duration chosen to reflect past research [4] that repetition of between 12 and 15 times is necessary to make a habit change, and 21 calendar days is 15 school days. The choice of schools within which to implement the program was influenced by the work of Pine et al [5] that states schools can be an optimum place for behavior change interventions where both parents and teachers may be involved in the intervention. The duration of 21 days was also chosen to avoid the program becoming overly onerous for the schools and teachers implementing the program.

Previous work has shown that the 21-day BDN program is effective in improving children’s toothbrushing knowledge and habits [6]. A study conducted in 10 countries with 7991 children aged between 2 and 12 years revealed that 25% more of the school children brushed their teeth twice a day at the close of the 21-day intervention. The program was found to be more effective among the 7 to 9 year age group.

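### The withdrawal rule removes children who miss more than 5 school days from the analysis, while the data exclusion and intention-to-treat statements keep them; following the withdrawal rule can bias the program effect.

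*Protocol article*

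**What the plan says.** Three sections of the protocol article deal with a child who is absent for more than 5 days.

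- Participant Withdrawal: "Children will be withdrawn from the study analysis if they miss more than 5 days of school during the 21-day intervention period". The check is the same in both arms: "School attendance during the 21-day period will be checked against the school register".
- Data Exclusion: "All school data will be used", and "Participants who missed more than 5 days (one school week) of the 21-day BDN program will have this information registered in the analysis". This is a flag. Nobody is removed.
- Statistical Analysis: "To minimize bias in the results, the intention to treat principle will be applied and every randomized participant will be analyzed". For missing values, "carrying the last data forward should be the best approach".

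Prior Work gives the length of the program and the reason for it: "repetition of between 12 and 15 times is necessary to make a habit change, and 21 calendar days is 15 school days".

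**The concern.** The withdrawal rule concerns membership of the analysis and not only continued follow-up. It is not limited to a per-protocol or sensitivity set, so it conflicts directly with the intention-to-treat statement. With both in the text, an analyst could choose the set after seeing the data.

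The choice matters because attendance is recorded after schools have been randomized. In an intervention school, a child who is often absent has missed program sessions. In a control school, which receives only toothpaste and toothbrushes, absence costs no program exposure. Removing frequent absentees therefore takes the least exposed children out of one arm and has no matching meaning in the other. Poor attenders may also differ in brushing for reasons unrelated to the program. The children who remain need not be the groups that randomization created.

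**Working it through.** **Step 1: which children each rule keeps.**

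| Section | Child missing more than 5 days | In the analysis? |
|---|---|---|
| Participant Withdrawal | withdrawn from analysis | No |
| Data Exclusion | absence registered | Yes |
| Statistical Analysis | intention to treat | Yes |

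The last two rules agree on who is analyzed, so there are two sets. No section ranks one rule above another.

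**Step 2: exposure of the removed children.** Prior Work equates 21 calendar days with 15 school days. Missing more than 5 means missing at least 6, so at most 15 − 6 = 9 days are attended. That is below the 12 to 15 repetitions which the same section regards as necessary for a habit change.

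**Step 3: possible size from lost exposure.** The article states no figure to reproduce. Inputs:

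- D, the difference among children who stay in after exclusion. The planning differences in Selection of Schools are used: 35 for Nigeria and 30 for Indonesia, read as percentage points (an assumption).
- f, the share of children missing more than 5 days. It is not given and is assumed equal in both arms.
- g, the fraction of the effect that absentees still gain. It is not given; 0 is the extreme case.

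The difference among all children is D × [1 − f(1 − g)], and the overstatement after exclusion is D × f(1 − g).

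To choose a range for f, assume mean daily attendance of 90% to 80%. The chance of missing more than 5 of 15 days is then 0.2% to 6% if days are independent (binomial). It is 6% to 18% if absences cluster within child with a correlation of 0.15 (beta-binomial).

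| f | Nigeria, g = 0 | Nigeria, g = 0.5 | Indonesia, g = 0 | Indonesia, g = 0.5 |
|---|---|---|---|---|
| 0.2% | 34.9 | 35.0 | 29.9 | 30.0 |
| 5% | 33.3 | 34.1 | 28.5 | 29.3 |
| 10% | 31.5 | 33.3 | 27.0 | 28.5 |
| 18% | 28.7 | 31.9 | 24.6 | 27.3 |

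Example: Nigeria, f = 10%, g = 0 gives 35 × 0.90 = 31.5, an overstatement of 3.5 points (35/31.5 − 1 = 11%). With g = 0.5 it is 35 × 0.95 = 33.25, an overstatement of 1.75 points (5%).

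**Step 4: can the direction reverse?** Suppose the program has no effect on brushing but halves absence, from f to f/2. Suppose absentees are 20 points worse (assumed) and are excluded in both arms. The control arm then contains only attenders. The intervention arm still contains children who would otherwise have been absent. The bias is −20 × (f/2)/(1 − f/2) points:

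- f = 5%: −20 × 0.025/0.975 = −0.5
- f = 10%: −20 × 0.05/0.95 = −1.1
- f = 20%: −20 × 0.10/0.90 = −2.2

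Under these assumptions the exclusion works against the program.

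**The case against.** The strongest reply is that the article already leans toward intention to treat. The two sections that govern the data and the analysis both keep these children, and one of them gives avoidance of bias as its reason. The withdrawal rule is a single sentence in a section on managing participants. This stands in part. It shows which way to reconcile the text, but the sentence names the analysis explicitly and nothing overrides it.

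Four stronger readings are tempting, and the article does not support them.

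- *A reader might count three analysis sets.* A flagged child stays in the data, so there are two.
- *A reader might infer that the primary result will be a per-protocol comparison labelled intention to treat.* That follows only if the analyst applies the withdrawal rule and keeps the label. The text leaves this possible but does not plan it.
- *A reader might say that the rule is worded differently for the two arms, because Data Exclusion counts days of a program that control schools do not have.* That sentence removes nobody. The rule that does remove children counts school days from the register, which both arms have. Its lack of neutrality comes from its link to program exposure.
- *A reader might infer that the effect is certainly inflated, by as much as 25%.* That figure needs 20% absence, which is above the 0.2% to 18% illustrated, and no benefit at all for children who may have attended 9 sessions. Parents also receive leaflets, so some benefit is plausible. That the program's rewards change attendance is conjecture, since the article does not tie them to attendance.

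**Conclusion.** The contradiction is real, is in the current text, and must be reconciled before analysis because it decides who enters the primary comparison. That conclusion rests on the wording alone and needs no assumption about absence.

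The consequence is conditional. Following the withdrawal rule can bias the program effect. Upward is the likeliest direction, because the least exposed intervention children are removed, but the bias could be negligible or reversed. The g = 0 columns are upper bounds for lost exposure at each absence rate, not estimates. They assume percentage-point differences, equal absence in both arms and no benefit to absentees. At 5% to 10% absence the overstatement is then at most about 1.8 to 3.5 points in Nigeria and 1.5 to 3.0 in Indonesia. It is half that if absentees gain half the effect, and under 0.1 point at 0.2% absence.

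**What to change.** In Participant Withdrawal, delete the provision that takes absent children out of the analysis. State that all enrolled children are analyzed in the arm assigned to their school, whatever their attendance, and that days missed are recorded from the school register in both arms. In Data Exclusion, word the registered item as school days missed, so that it applies to control schools too. If an attendance-based exclusion is wanted, confine it to a supplementary analysis labelled as a non-randomized comparison.

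The cost is small: a few sentences in the protocol, carried into the analysis plan. No new data are needed, because attendance is already to be checked against the register. The estimate may become slightly less favourable to the program.
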